|--------------|-------------------------------------------------------------------------------------------------------------------------------------------------------------------------------------------------------------|----------------------|-------------------------------------------------------------------------------------------------------------------------------------------------------------------------------------------------------------------------------------------------|
|              | Percentage of people from key population who have been screened for STI in the past 12 months (prior to participation in the survey)                                                                        | WHO SRH-4            | Num: Number of respondents who have been screened for STI in the past 12 months

Denom: Number of people interviewed                                                                                                                      |
|              | Percentage of people from key population who have received information on HIV, AIDS, condoms or safe sex in the past 12 months (from an outreach or health worker)?                                         |                      | Num: Number of respondents who have received information on HIV, AIDS, condoms or safe sex in the past 12 months?

Denom: Number of people interviewed                                                                                    |
|              | Key population reporting they have received a combined set of health sector interventions                                                                                                                   | WHO PKG-2            | Condoms; lubricant; information on condom use and safe sex; HTC; STI screening;                                                                                                                                                                 |
|              | Proportion of key populations reached with individual and/or small group level HIV preventive interventions that are based on evidence and/or meet the minimum standard required (KP_PREV/CUSTOM INDICATOR) | PMP 1.1b             | Num: Number of respondents who have received any of the above interventions in the past 12 months

Denom: Number of people interviewed                                                                                                    |

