|--------------|-----------------------------------------------------------------------------------------------------|------------------|--------------------------------------------------------------------------------------------------------------------------------------------------------------------------------------------------------------------------------------------------------|
|              | Percentage of men reporting the use of a condom the last time they had anal sex with a male partner | 1.12; O-4e, O-4g | 
Num: Number of male or transgender respondents who report condom use at last anal sex with a male partner in the last 12 months.
 
Denom: Number of male respondents who have had sex with at least one male partner in the past 6 months.
 |
| Stigma       | Percentage of key populations reporting stigma and discrimination                                   | O-5a             | 
Num: Number of people who report experiencing stigma or discrimination due to their sexual orientation, work or HIV status
 
Denom: Number of people interviewed
                                                                           |
|              | Percentage of people from key populations who have experienced discrimination by health workers     | NEEDS.7          | 
Num: Number of people who report experiencing discrimination by a health care worker
 
Denom: Number of people interviewed
                                                                                                                 |

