| C8                                        | Have you had sex with a person in the past 12 months who you never had sex with before? That is, you had sex with him or her the first time in the past 12 months. | Yes
1         | No
2 |
| C9                                        | Have you had sex with more than 10 people in the past 12 months?                                                                                                   | Yes
1         | No
2 |
| C10                                       | Have you had anal sex in the past 12 months with a man?                                                                                                            | Yes
1         | No
2 |
| C10A                                      | Did you use a condom use with your last male partner?                                                                                                              | Yes
1         | No
2 |
| NO.                                | QUESTION                                                                                                                                                    | RESPONSE  |         |
| C11                                       | Have you received money in exchange for sex in the past 12 months?                                                                                                 | Yes
1         | No
2 |
| C11A                                      | Did you use a condom use with your last client?                                                                                                                    | Yes
1         | No
2 |
| C12                                       | Have you ever received money in exchange for sex?
IF NO: GO TO C14.                                                                                             | Yes
1         | No
2 |
| C13                                       | How old were you the first time you received money in exchange for sex?
LEAVE BLANK IF NOT APPLICABLE.                                                          | WRITE AGE: _____ |         |
| C14                                       | In the last 12 months, have you given someone money to have sex?                                                                                                   | Yes
1         | No
2 |

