| QUESTIONS ABOUT ACCESS TO SERVICES |                                                                                                                                                                    |                  |         |
| C15                                       | If you wanted a condom, would it be easy to get one?                                                                                                               | Yes
1         | No
2 |
| C16                                       | In the past 12 months, has an outreach worker such as a peer educator given you a condom?                                                                          | Yes              | No      |

|            |                                                                                                                                                               |                                                                                   |
|------------|---------------------------------------------------------------------------------------------------------------------------------------------------------------|-----------------------------------------------------------------------------------|
|            |                                                                                                                                                               | 1 2                                                                               |
| C17        | Do you have a condom with you now?                                                                                                                            | Yes No
1 2                                                                     |
| C18A       | In the last 12 months, have you had any burning when you pee, or discharge from your penis or vagina or anus, or sores on your genitals?                      | Yes No
1 2                                                                     |
| C18B       | IF YES: In the last 12 months, have you sought care for any of these symptoms at a public or private clinic?
IF NOT APPLICABLE (C18=2) THEN CIRCLE 9 (NA). | Yes No NA
1 2 9                                                                |

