| C18C       | In the past 12 months Have you been discriminated against by a healthcare worker?                                                                             | Yes No NA
1 2 9                                                                |
| C18D       | At what type of facility did you seek care?                                                                                                                   | dedicated to HIV
general health care
outreach services
referral facility |
| C19        | IF RESPONDENT IS MALE, ASK: Are you circumcised?
IF FEMALE, CIRCLE 9 (NA).                                                                                 | Yes No NA
1 2 9                                                                |
| C20        | How many servings of alcohol have you had in the past 24 hours? A serving is a bottle of beer or a shot of alcohol.                                           | NUMBER:____                                                                       |
| C21        | In the past 12 months, have you received information about HIV or AIDS from an outreach worker at this site?                                                  | Yes No
1 2                                                                     |
| NO. | QUESTION                                                                                                                                               | RESPONSE                                                                   |
| C22        | In the past 12 months, have you received information about HIV or AIDS from the radio?                                                                        | Yes No
1 2                                                                     |

|            |                                                                                                                                                                                                  |                                                 |             |
|------------|--------------------------------------------------------------------------------------------------------------------------------------------------------------------------------------------------|-------------------------------------------------|-------------|

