| C23        | In the past 12 months, have you received information about HIV or AIDS from any health worker?                                                                                                   | Yes
1                                        | No
2     |
| C24        | Are you currently seeing a health worker for an HIV infection?                                                                                                                                   | Yes
1                                        | No
2     |
| C25        | Are you currently taking antiretroviral (ART) drugs to treat an HIV infection?                                                                                                                   | Yes
1                                        | No
2     |
| C26        | Now I have a few questions about HIV tests. Have you ever had an HIV test?
IF NO: GO TO C31.                                                                                                  | Yes
1                                        | No
2     |
| C27        | Has a medical provider ever told you that you are infected with HIV, based on an HIV test result? IF NO GO TO C29.                                                                               | Yes
1                                        | No
2     |
| C28        | Think about the first time a medical provider told you that you that you were infected with HIV. Did this occur in the past 3 months? Past 12 months? Or longer ago? IF LONGER AGO, SKIP TO C31. | Past 3 Months
Past 4-12 months
Longer ago | 1
2
3 |
| C29        | Have you been tested for HIV in the past 12 months?
IF NO, GO TO C31.                                                                                                                         | Yes
1                                        | No
2     |
| C30        | IF YES (C29=1) ASK: The last time you were tested, did you get your test result?                                                                                                                 | Yes
1                                        | No
2     |
| C31        | Some people have tried injecting drugs using a needle and syringe. Have you injected any non-prescription drug in the past 12 months?                                                            | Yes
1                                        | No
2     |

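### Form C records outreach information only at the interview site and omits condoms and safe sex, so a Table 4 coverage row is undercounted; its condom item C10A is also ambiguous about anal sex

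*Protocol*

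**What the plan says.** **Information row.** In Section VIII.B, Table 4 (Reach people, Coverage), the indicator is the percentage of key-population members "who have received information on HIV, AIDS, condoms or safe sex in the past 12 months (from an outreach or health worker". The row sets no limit on place. Two later rows draw on the same information: the combined package (WHO PKG-2), whose list includes information on condom use and safe sex, and PMP 1.1b, which counts receipt of any of the preceding interventions.

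Form C (Appendix 4) has two items on information from workers, both over 12 months:

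- C21: "have you received information about HIV or AIDS from an outreach worker at this site"
- C23: "have you received information about HIV or AIDS from any health worker"

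C16, also about outreach, has no site limit: "has an outreach worker such as a peer educator given you a condom".

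**Condom row.** Table 4 (Behavior) has the numerator "Number of male or transgender respondents who report condom use at last anal sex with a male partner in the last 12 months". Its denominator is male respondents with any sex with a man over six months. In Form C, C10 asks "Have you had anal sex in the past 12 months with a man" and C10A follows with "Did you use a condom use with your last male partner". C10A names no act, and no skip from C10 is printed. The PLACE key-population criteria in Section VI.C admit men whose contact with men in the past year was oral sex only.

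**The concern.** A coverage indicator is only as wide as the question behind it. The row credits outreach contact anywhere, but the form credits it only at the venue where the respondent happens to be interviewed. The protocol itself expects people to use more than one venue: the size estimation in Section VIII.C adjusts for mobility and multiple sites, and C4 asks how many other places are visited that day. Someone informed by a peer educator at another bar, and by no health worker, would be scored as not reached. So would someone told only about condoms or safe sex.

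Coverage of prevention services is part of the study aim (Section V), and Section VIII.B names information among the coverage indicators. An answer that was never asked for cannot be recovered in analysis, so a later analysis plan cannot repair this.

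For condoms, the risk is that some respondents answer C10A about a partner or act other than their last anal sex. The reported figure would then describe something different from its label.

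**Working it through.** The protocol gives no rates for either indicator, so there is no planned figure to reproduce. The check is a comparison of wording, followed by illustrations on stated assumptions.

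**1. Information row, side by side**

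| Element | Table 4 row | C21 | C23 |
|---|---|---|---|
| Source | outreach or health worker | outreach worker | health worker |
| Place | any | interview site only | any |
| Topics | HIV, AIDS, condoms, safe sex | HIV, AIDS | HIV, AIDS |

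Scored as C21 or C23 = yes, everyone counted truly meets the row, because HIV and AIDS are among its topics. Two groups who meet it are lost: those informed by outreach elsewhere only and by no health worker, and those informed only about condoms or safe sex. The error is therefore downward or zero.

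**2. Size of the site-limit loss (all inputs assumed)**

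Let a = share with outreach information at this site, b = share with it only elsewhere, and h = share informed by a health worker, independent of outreach.

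- Recorded: 1 − (1 − a)(1 − h)
- True: 1 − (1 − a − b)(1 − h)
- Shortfall: b(1 − h); a drops out

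With a = 20%, b = 15%, h = 30%:

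- Recorded: 1 − 0.80 × 0.70 = 44.0%
- True: 1 − 0.65 × 0.70 = 54.5%
- Shortfall: 0.15 × 0.70 = 10.5 points

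At b = 5% the shortfall is 0.05 × 0.70 = 3.5 points. At b = 25% it is 0.25 × 0.70 = 17.5 points. At b = 0 it is zero. The loss from omitted topics would come on top and is not sized here.

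For scale, the simple-random-sampling 95% half-width at 50% is 1.96 × √(0.25/600) = 4.0 points for the 600 sex workers or 600 MSM expected in Luanda, and 1.96 × √(0.25/200) = 6.9 points for the 200 transgender women. Clustering by venue is ignored. A larger sample would not shrink the shortfall.

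**3. Condom row**

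Let p = condom use at last anal sex, f = share whose C10A answer refers to some other act, and q = condom use at that act. The error is f(q − p). With p = 50% and q from 20% to 80% (assumed):

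| f | Error range (points) |
|---|---|
| 0% | 0 |
| 10% | −3 to +3 |
| 20% | −6 to +6 |
| 30% | −9 to +9 |

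The error is zero if q = p, or if respondents take C10A to mean the anal sex just asked about in C10. The documents fix none of f, q or p.

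**4. Condom denominator**

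The numerator concerns anal sex over 12 months and the denominator any sex with a man over six. Form C has no six-month item on male partners: C6 covers four weeks and C10 covers 12 months. The denominator cannot be formed from Form C, and men with oral sex only would sit in it without being able to enter the numerator.

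**The case against.** - **Few people may be missed under C21.** The loss is confined to those reached by outreach only off site and by no health worker. Respondents may count outreach staff as health workers under C23; community health workers are among the protocol's own informant types. The shortfall could be near zero. This stands as a limit on size. It does not remove the site limit or supply the missing topics.
- **The source limit is only in the row's title.** The Measure cell names no source. Read that way the row is wider still, and C21 with C23 falls further short of it.
- **C10A reads naturally as a follow-up to C10.** C11 and C11A show the same pattern, and oral-only men can be removed with C10 = no. This largely stands. A reader might infer that the condom row is also biased, and biased low: if 10% to 40% of last partners were oral-only with 10% condom use, a true 60% would read as 55% to 40%. The documents do not support that. The direction comes entirely from the assumed 10%, and whether any error exists depends on how respondents read the item.
- **The objectives do not name information.** A reader might infer that the service gaps listed in Section V would be overstated. That list names HIV testing and counselling, condoms and STI management, and C16 asks about outreach condoms without a site limit. The support lies in the general aim in Section V and in Section VIII.B.
- **Wording will be piloted.** Section VI.C (Step 1) plans a pilot with revision and Section VII.E a pre-test that replaces unclear questions. That may catch C10A. C21 is perfectly clear, so a clarity check need not flag it.

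**Conclusion.** The point holds for the information row. Following Form C as printed, that row can only be undercounted or, at best, unaffected. The size is unknown; 3.5 to 17.5 points follows only if 5% to 25% were reached by outreach solely elsewhere and 30% independently heard from a health worker.

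The site limit carries into the two package rows in the same direction. In PMP 1.1b it matters only for people who received none of the other interventions. PKG-2 has a further gap, because neither item asks about the condom and safe-sex information that it lists.

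For condom use, the supportable conclusion is narrower. C10A is ambiguous and may introduce an error of unknown sign, and the row's numerator and denominator do not match each other.

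All of this concerns the PLACE Form C. Appendix 5, the Cabinda questionnaire, is not reproduced, so no conclusion extends to the RDS survey.

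**What to change.** 1. **C21:** ask about *information about HIV, AIDS, condoms or safe sex from an outreach worker, at any place*. Keep an on-site follow-up only if site-level coverage is wanted.
2. **C23:** add condoms and safe sex to the topics.
3. **C10A:** ask *The last time you had anal sex with a man, was a condom used?*, with a printed skip unless C10 = yes.
4. **Table 4 condom row:** replace the six-month any-sex denominator with respondents who had anal sex with a man in the past 12 months (C10 = yes), naming the same male and transgender respondents as the numerator. Rewording C10A alone would leave this row mismatched.

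The cost is three reworded items, one skip instruction and one line of Table 4, made before translation and the pilot. Interview time is essentially unchanged unless the optional follow-up is added.

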**Table 4 Key indicators targeting MSM used by FHI, UNAIDS, and PEPFAR for behavioral surveillance purposes.**

| Cascade Step      | Indicator                                                                                                                                   | Indicator # | Measure                                                                                                                                                    |
|--------------------------|----------------------------------------------------------------------------------------------------------------------------------------------------|--------------------|-------------------------------------------------------------------------------------------------------------------------------------------------------------------|
| Identify population size | Estimated total number of key populations in the program geographic area (denominator for KP_PREV)                                                 | PMP 1.1b (denom.)  |                                                                                                                                                                   |
| Reach people, Coverage   | Percentage of people from key population who have received free condoms and lubricant in the past 12 months                                        | WHO CCP-3, CCP-5   | Num: Number of respondents who received free condoms and lubricant in the past 12 months

Denom: Number of people interviewed                               |
|                          | Percentage of respondents who have been tested for HIV during the last 12 months and who know their results (prior to participation in the survey) | GARPR 1.9 & 1.13   | Numerator: Number of respondents who have been tested for HIV during the last 12 months and who know the results.

Denominator: Total number of respondents |

Programmatic Mapping and HIV/STI Prevalence Study among Key Populations in Angola

| Cascade Step | Indicator                                                                                                                                                                                                   | Indicator #          | Measure                                                                                                                                                                                                                                         |

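### Form C does not ask people diagnosed over a year ago about HIV testing in the past 12 months, but Table 4 keeps them in the denominator, so testing coverage can be understated and never overstated

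*Protocol*

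**What the plan says.** The indicator is defined in Section VIII.B, Table 4, in the row for GARPR 1.9 & 1.13: "Percentage of respondents who have been tested for HIV during the last 12 months and who know their results (prior to participation in the survey"). The numerator is "Number of respondents who have been tested for HIV during the last 12 months and who know the results". The denominator is given as "Denominator: Total number of respondents", with no exclusion for people already known to be HIV-positive.

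The data come from Appendix 4, Form C:

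- C26 asks about lifetime testing and routes the never-tested out: "Have you ever had an HIV test? IF NO: GO TO C31".
- C27 asks whether a medical provider has ever told the respondent of an HIV infection. A no goes to C29.
- C28, for those told, asks whether the first time was in the past 3 months, 4 to 12 months ago, or longer ago, and adds "IF LONGER AGO, SKIP TO C31".
- C29 asks "Have you been tested for HIV in the past 12 months".
- C30 asks "The last time you were tested, did you get your test result".

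No other Form C item records a test in the past 12 months or receipt of a result. C24 and C25 cover current care and antiretroviral treatment.

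**The concern.** The form and the table treat the same people differently. Form C takes those diagnosed over a year ago out of the recent-testing questions, while Table 4 keeps them in the indicator. They add to the denominator and cannot enter the numerator, whatever their testing history.

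HIV testing is one of the prevention-coverage measures named in Section VIII.B, and gaps in testing and counselling services are part of the objectives in Section V. An error that runs in one direction, and that varies with HIV prevalence and with how long ago people were diagnosed, could differ between sex workers, MSM and transgender women, and between provinces.

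The gap arises at data collection. An analysis plan can remove these people from the denominator, but it cannot compute the indicator as Table 4 defines it, because the answers will not exist.

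**Working it through.** The protocol states no figure on this point, so there is none to reproduce. The check has three steps.

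**1. Routing through C26 to C31**

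| Respondent | Route | C29/C30 asked? | Can enter numerator? | In denominator? |
|---|---|---|---|---|
| Never tested | C26 to C31 | No | No, correctly | Yes |
| Tested, never told positive | C27 to C29 | Yes | Yes | Yes |
| First told in past 12 months | C28 to C29 | Yes | Yes | Yes |
| First told over 12 months ago | C28 to C31 | No | No, even if retested with a result | Yes |

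Only the last row is a mismatch. C26 to C28 separate it from the never-tested, whose C29 and C30 are also blank.

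**2. Size of the loss**

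Let T be the proportion tested with a result among all other respondents.

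- Indicator as collected: (1 − q) × T
- Indicator if C29 and C30 were asked of everyone ever tested: (1 − q) × T + q × r
- Loss: q × r, which is never negative and does not depend on T

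Inputs:

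- HIV prevalence 3.8% to 10.5%, MSM in Luanda (Section IV). The 8.5% given there for women in transactional sex in Cunene lies inside this range.
- Share of positives diagnosed over 12 months ago: assumed 25% to 75%.
- r: not in the documents and not collected by the form, so shown at 0, 10% and 60%.

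q runs from 0.038 × 0.25 = 0.0095 to 0.105 × 0.75 = 0.0788, or about 1% to 8%. Among 600 MSM in Luanda that is about 6 to 47 people.

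| r | Loss at q = 0.0095 | Loss at q = 0.0788 |
|---|---|---|
| 0 | 0 | 0 |
| 10% | 0.1 points | 0.8 points |
| 60% | 0.6 points | 4.7 points |

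At 8.5% prevalence with half of positives diagnosed that long ago, q = 0.0425, and the loss is 0.4 points at r = 10% and 2.6 points at r = 60%.

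**3. What deleting the skip does to comparisons**

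Take two groups with the same T = 50% (assumed), one with q = 0.0095 and one with q = 0.0788, and r = 10% in both.

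- As collected: 0.9905 × 50% = 49.5% and 0.9212 × 50% = 46.1%, a gap of about 3.5 points.
- With C29 and C30 asked of all: 49.5% + 0.1 = 49.6% and 46.1% + 0.8 = 46.9%, a gap of about 2.8 points.
- Restricted to respondents not diagnosed over 12 months ago: 50% and 50%, no gap.

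Most of the gap comes from the all-respondents denominator, not from the skip.

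**The case against.** Several objections have force.

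- **No error for those not retested.** Someone diagnosed long ago and not tested in the past year is correctly outside the numerator on the literal definition. A reader might infer that coverage is definitely understated, or that it shrinks in proportion to q. The proportional reading assumes that known positives are retested as often as everyone else, and nothing in the protocol supports that. The loss is q × r and may be zero.
- **Past case-finding.** A reader might blame the skip for a group with better past diagnosis showing lower coverage. Step 3 shows that this effect largely remains once the skip is gone.
- **Combined package.** A reader might assume that the combined-package row in Table 4 inherits the loss. That row lists testing and counselling with no time window and no link to a form item, so it is affected only if the component is taken from C29 and C30.
- **Coding.** The protocol does not say that skipped respondents are coded as untested. An analysis plan could set another rule, and C27 and C28 already allow the restricted version to be computed. It still could not produce the indicator as written.
- **Intent and later revision.** The skip may be deliberate, since known positives are followed through the diagnosis, care and treatment items, and the awareness-of-status row is unaffected. The instruments are also to be piloted and pre-tested (Sections VI.C and VII.A). That lowers the weight of the point but does not remove the mismatch.
- **Precision.** At 60% coverage the simple-random 95% half-width is 1.96 × √(0.6 × 0.4 / 600) = 3.9 points for 600 people and 6.8 points for 200, before clustering. At low r the loss is well inside this, so a claim of materially distorted comparisons would go too far.

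**Conclusion.** The mismatch is real: for one identifiable group, Form C does not collect what the Table 4 indicator needs, and Table 4 does not say how that group is handled. From this cause the indicator can be too low and never too high. The loss runs from zero to about 4.7 percentage points over the range shown, and is below 1 point if retesting of known positives is uncommon (r = 10%). These sizes rest on the assumed share of positives diagnosed over a year ago, on the assumed r, and on the background prevalence applying to the surveyed groups.

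The point covers Form C only; the Cabinda questionnaire is not shown. It is a minor point, worth correcting because the missing answers cannot be recovered after fieldwork.

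**What to change.** Delete the skip instruction at C28, so that C29 and C30 are asked of everyone ever tested. In the GARPR 1.9 & 1.13 row of Table 4, report the indicator on two lines: among all respondents, as now defined, and among respondents not diagnosed more than 12 months ago, identified from C27 and C28. The first change makes the stated indicator computable. The second deals with the effect of past case-finding on comparisons. It would also help to name the item that supplies the testing component of the combined-package row.

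The cost is two yes/no questions for a few percent of respondents and one extra table line.
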